## Abstract

**Background:**

Skin cancer is the most prevalent yet most preventable cancer in the US. While protecting oneself from ultraviolet radiation (UVR) can largely reduce risk, rates of unprotected sun exposure remain high. Because the desire to be tan often outweighs health concerns among sunbathers, very few interventions have been successful at reducing sunbathing behavior. Sunless tanning (self-tanners and spray tans), a method of achieving the suntanned look without UVR exposure, might be an effective supplement to prevention interventions.

**Methods and Design:**

This cluster randomized trial will examine whether a beach-based intervention that promotes sunless tanning as a substitute for sunbathing and includes sun damage imaging and sun safety recommendations is superior to a questionnaire only control group in reducing sunbathing frequency. Female beach visitors (N = 250) will be recruited from 2 public beaches in eastern Massachusetts. Beach site will be the unit of randomization. Follow-up assessment will occur at the end of the summer (1-month following intervention) and 1 year later. The primary outcome is average sunbathing time per week. The study was designed to provide 90% power for detecting a difference of .70 hours between conditions (standard deviation of 2.0) at 1-year with an intra-cluster correlation coefficient of 0.01 and assuming a 25% rate of loss to follow-up. Secondary outcomes include frequency of sunburns, use of sunless tanning products, and sun protection behavior.

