### Sample size considerations and statistical analyses

#### Sample size

The two-arm cluster randomized trial is designed to have at least 80% power at a 5% significance level to test the hypothesized intervention effects at 1- and 12-months on the primary outcome: average time spent sunbathing per week. Means and standard deviations from our previous investigation were used for sample size estimate. With the proposed analytic method, we estimated the required sample sizes for three testing scenarios, i.e., changes between baseline and 1 month, changes between baseline and 12 months, and the joint test involving all three time points (see Table 1). Sample sizes were calculated using the method developed by Frison [36]. Given the possibility that individuals recruited in the same day may show correlation between each other (intra-cluster correlation or ICC), we adjusted the sample sizes with assumed intra-cluster correlation coefficient of 0.01 with method of Garrett [37]. We anticipate a relatively low level of dependency should it exist (ρ = .01) given that individuals at the beach on one day may not be strongly different from individuals visiting the same location the next day. The estimated minimum sample sizes are presented in the Table 1 with the assumed parameters, specifically, the expected mean difference between the two arms after intervention is assumed to be 0.75 and 0.70 hours sunbathing per week at 1 and 12 months, the within-subject correlation is assumed to be 0.50 at 1 month and 0.45 at 12 months. These estimates allow for withdrawal and loss to follow up of 15% and 25% at 1 and 12 months.

**Table 1 T1:** Sample size for three test scenarios for primary outcome: hours spent sunbathing per week

	Mean (SD)									
									
Test Scenarios	Control	Post-Intervention	Expected difference in mean	Within-subject correlation	No. of cluster (day)	Subject/cluster	Intra-cluster correlation	Minimum size/group	Dropout rate	Adjusted minimum total size
A (0–2 month)	2.10 (2.0)	1.35 (2.0)	0.75	0.50	16	12	0.01	94	0.15	**222**
B (0–12 month)	2.10 (2.0)	1.40 (2.0)	0.70	0.50	16	14	0.01	118	0.25	**314**
C (0–2–12 month)	2.10 (2.0)	1.38 (2.0)	0.72	0.50	16	9	0.01	66	0.25	**176**

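### The abstract's 90% power for a 0.70-hour difference at 1 year does not hold with N = 250: Table 1 requires 314 for 80%, and 250 gives about 72–75%

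*Protocol article*

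**What the plan says.** The abstract (Methods and Design) gives the sample size, "Female beach visitors (N = 250) will be recruited from 2 public beaches in eastern Massachusetts", and then the power: "The study was designed to provide 90% power for detecting a difference of .70 hours between conditions (standard deviation of 2.0) at 1-year". It adds that this allows for an "intra-cluster correlation coefficient of 0.01 and assuming a 25% rate of loss to follow-up".

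The Sample size section gives a different power level: the trial "designed to have at least 80% power at a 5% significance level to test the hypothesized intervention effects at 1- and 12-months". The expected differences are "assumed to be 0.75 and 0.70 hours sunbathing per week at 1 and 12 months". On correlation it says "the within-subject correlation is assumed to be 0.50 at 1 month and 0.45 at 12 months".

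Table 1 lists three scenarios, all with SD 2.0, ICC 0.01 and a printed within-subject correlation of 0.50:

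| Row | Contrast | Difference | Subjects per cluster | Minimum per group | Loss | Total |
|---|---|---|---|---|---|---|
| A | baseline to first follow-up | 0.75 | 12 | 94 | 15% | 222 |
| B | baseline to 12 months | 0.70 | 14 | 118 | 25% | 314 |
| C | all three time points | 0.72 | 9 | 66 | 25% | 176 |

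Neither N = 250 nor 90% power appears in the Sample size section or in Table 1.

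**The concern.** The abstract's inputs (0.70 h, SD 2.0, 1 year, ICC 0.01, 25% loss) are those of row B. For that row the article gives 314 participants and at least 80% power in one place, and 250 participants and 90% power in another. Both cannot be right, because the smaller sample is credited with the higher power.

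The abstract is the statement of the design that most readers will use. If it is wrong, a null result at 1 year will be read as coming from a trial with a 10% chance of missing the planned effect, when the actual chance is more than twice that.

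Row B also disagrees with the text on the 12-month correlation (0.50 printed, 0.45 in the text), so the reader cannot tell which value produced the 12-month requirement.

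**Working it through.** **Inputs.** SD 2.0, ICC 0.01, the differences, losses and cluster sizes come from Table 1. The correlations come from the table (0.50) and the text (0.45 at 12 months). N = 250 comes from the abstract. Three assumptions are needed: a two-sided 5% test, equal allocation, and 16 clusters in total. The third fits the table: twice the per-group size divided by 16 is 11.75, 14.75 and 8.25, against printed cluster sizes of 12, 14 and 9.

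**Step 1: reproduce Table 1.** For a baseline-adjusted comparison,

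n per group = 2 (z₀.₉₇₅ + z_power)² SD² f / d² × [1 + (m − 1) × 0.01],

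with f = 1 − r² for one follow-up and f = (1 + r)/2 − r² for the average of two follow-ups.

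| Row | f | At 80% power | At 90% power | Printed |
|---|---|---|---|---|
| A, r = 0.50 | 0.75 | 83.7 × 1.11 = 92.9 | 124 | 94 |
| B, r = 0.45 | 0.7975 | 102.2 × 1.13 = 115.5 | 155 | 118 |
| B, r = 0.50 | 0.75 | 96.1 × 1.13 = 108.6 | 145 | 118 |
| C, r = 0.50 | 0.50 | 60.6 × 1.08 = 65.4 | 88 | 66 |

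The loss adjustment also matches: 188/0.85 = 221.2, 236/0.75 = 314.7 and 132/0.75 = 176. Table 1 is therefore an 80% table, and no row fits 90%. Row B comes close to its printed value with r = 0.45 and not with the 0.50 shown in that row.

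**Step 2: 12-month power with N = 250.**

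- Analysed per arm: 125 × 0.75 = 93.75.
- Cluster size: 187.5/16 = 11.7, so the design effect is 1 + 10.7 × 0.01 = 1.107.
- r = 0.50: SE = 2 × √(2 × 0.75 × 1.107/93.75) = 0.266; 0.70/0.266 = 2.63; power = Φ(2.63 − 1.96) ≈ 75%.
- r = 0.45: SE = 0.2745; 0.70/0.2745 = 2.55; power ≈ 72%.
- Scaling straight from the printed 118 per group at 80%: 2.80 × √(93.75/118) = 2.50, power ≈ 70%.

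With 16 clusters, 90% power at 12 months needs a total of about 405 (r = 0.50) to 436 (r = 0.45). Scaling from 118 gives 118 × (3.2416/2.8016)² × 2/0.75 ≈ 421. At N = 250 the difference detectable with 90% power is 3.24 × 0.266 = 0.86 h to 3.24 × 0.2745 = 0.89 h.

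**Step 3: other contrasts at N = 250.**

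- First follow-up, 0.75 h, 15% loss: 106.25 per arm, design effect 1.123, SE = 0.252, power ≈ 85%.
- Average of both follow-ups (f = 0.50), 25% loss: SE = 0.217, power ≈ 90% for 0.70 h and 91% for 0.72 h.

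**Step 4: try to recover 90% at 1 year.** Two-sided with clustering ignored gives 77–79%. Two-sided with clustering and all loss ignored gives 87–89%. One-sided, unclustered, with 25% loss gives at most 87%. A one-sided test with no loss does reach about 90% (91% with 16 clusters and r = 0.50). The abstract, however, says the 25% loss is included, and one-sided 90% does not fit row A (102 per group against 94).

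**The case against.** The strongest reply is that 1 year is not the only primary contrast. The Research goals name both follow-ups, and the analysis plan tests the primary hypothesis in one model with baseline, 1 month and 1 year through the group-by-time interaction. Row C is the three-time-point scenario, and N = 250 exceeds both its 176 and row A's 222. On this view a sound power figure was attached to the wrong contrast in an abstract. That explanation is plausible and means the design as a whole is not undermined. It does not make the printed statement true, since the abstract specifies 1 year.

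A second reply is that 72–75% is too precise, and this stands in part. The figure rests on 16 clusters in total, baseline adjustment and a normal reference:

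- If the 16 days at two beaches are counted as 32 beach-days, power is 75–77%.
- A t reference on 14 degrees of freedom gives about 66–69%.
- A change-score contrast, arguably closer to an interaction test with baseline as a time level, gives about 58–65% over the two cluster counts.

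All of these stay below 80%, so they affect the replacement figure and not the error. The same caution applies to the 90% for the averaged contrast: it falls to about 85% for 0.70 h on the t reference, and to about 75–77% (0.70–0.72 h) as a change score.

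Finally, r = 0.45 does not give exactly 118 in row B (115.5 by the formula above). It is the likely source, but this is not proven.

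**Conclusion.** The point holds. The 90% power at 1 year contradicts the article's own Table 1, which asks for 314 participants to reach 80% with the same inputs. N = 250 falls short of that and corresponds to no row.

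Under Table 1's own method, with a two-sided 5% test, equal arms, 16 clusters in total and 25% loss, the 1-year power is 72–75%. The abstract therefore overstates it by 15 to 18 points. Scaling from the printed 118 per group, or counting 32 beach-days, widens the range to about 70–77%. The chance of missing a true 0.70 h difference is then roughly 23–30%, against the 10% implied. That the 90% came from the averaged three-time-point scenario is an inference, and the correction does not depend on it.

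The mismatch between 0.45 and 0.50 in row B is a smaller, separate inconsistency in the same calculation.

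**What to change.** 1. In the abstract, replace the 90% with the 1-year power for N = 250 (about 72–75% for 0.70 h), or attach the 90% explicitly to the three-time-point test and no longer to 1 year.
2. In the Sample size section, say which scenario N = 250 was chosen to satisfy. State the power it gives for each: about 85% for 0.75 h at 1 month, about 72–75% for 0.70 h at 12 months, and about 90% for the average of the two follow-ups. Acknowledge that it is below row B's 314.
3. Beside these figures, state the assumptions: number of clusters and whether they are days or beach-days, baseline adjustment, two-sided test, and reference distribution.
4. Reconcile the 12-month correlation between the text and row B. The printed 118 per group points to 0.45; confirm this against the original calculation.

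The cost is wording and one table entry. Recruitment and the primary contrast need not change. The only loss is a less favourable power statement for 1 year.

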**Discussion:**

Interventions might be improved by promoting behavioral substitutes for sun exposure, such as sunless tanners, that create a tanned look without exposure to UVR.

**Trial registration:**

NCT00403377

## Background

Ultraviolet radiation (UVR) from the sun is linked to more cancers worldwide than any other carcinogen.[1] Because skin cancer, the most prevalent cancer in the US [2], is largely attributable to UV exposure, it is largely preventable [3,4]. Prevention via avoidance of UVR seems like a simple solution, but rates of unprotected sun exposure remain quite high [5].

The belief that a suntan enhances physical attractiveness is a strong predictor of prolonged unprotected sun exposure [6-10]. Tanned images in the media play a big role in reinforcing the value of a tanned appearance [11]. The social norm for the attractiveness of a tanned appearance is difficult to change given the: 1) long history of this belief in the American culture, and 2) the number of tanned media images saturating the public [12]. Individuals who value being tan have been particularly resistant to educational messages about skin cancer prevention [13-15]. Comprehensive interventions that include education, sun damage imaging, free sunscreen, signage, and/or shade structures have been more successful at promoting sun protection than purely educational interventions although such interventions target outdoor recreationers [16-19], college students [20-22], or outdoor workers [23] and have not been examined among high risk groups such as intentional sunbathers. Beach-based interventions specifically targeting sunbathers with instant sun damage imaging which increases the saliency of sun-related skin damage have been somewhat effective [24,25]. Results have shown significant increases in sun protection, but mixed outcomes on sunbathing behavior. Beach visitors exposed to such interventions increase their use of sunscreen perhaps in attempt to tan 'safely' (i.e., without burning), but do not appear to reduce their sunbathing. This false sense of security might perpetuate further sun exposure.

A different approach to prevention would be to attempt to reduce sun exposure among sunbathers without battling their motivation to be tan. The promotion of behavioral substitutes, products that provide a safe, alternate route to achieving a tan, might preclude the need to sunbathe and result in reduced risk behavior. Increasingly popular over-the-counter sunless tanning products (e.g., self-tanners, spray tans) may be a substitute for sun exposure. Sunless tanning products come in the form of creams, foams, and sprays to be applied directly to the skin by the consumer or a professional. They contain dihydroxyacetone (DHA), a colorless vegetable-derived sugar that interacts with dead surface cells in the epidermis, thereby staining the skin a tan color [26]. The US Food and Drug Administration (FDA) approved DHA as a color additive for use in cosmetics in 1973 [27]. Sunless tanning products containing DHA can be obtained over the counter or professionally applied to the entire body in salons. The tan produced by these products cannot be washed off with soap and water like make-up or bronzers, which produce a darkening of the skin via water-soluble colorants [28]. Like a suntan, the effect of sunless tanning products is temporary, because as dead skin cells naturally slough off, the color fades and disappears within a few days unless the product is reapplied. Overall, sunless tanning products are associated with negligible health risks compared to direct sun exposure. DHA is both nontoxic [29] and hypoallergenic [30] but is not a significant source of sun protection. Although one might suspect that use of sunless tanning could lead to a false sense of security in terms of sun protection, cross-sectional studies have reported higher rates of sunscreen use among individuals who use sunless tanning [31-33]. Further investigation is needed to determine whether sunbathers would be willing to substitute sunless tanning products for a UV tan and if promoting sunless tanning reduces sunbathing.

### Research goals

In the present study, the efficacy of a multi-component beach-based intervention that features sunless tanning among female beach visitors will be tested. The intervention will promote sunless tanning as a substitute for sunbathing and include sun damage imaging and sun safety recommendations. The primary outcome will be sunbathing at 1-, and 12-months follow-up and a questionnaire-only control group will be employed for comparison. Secondary outcomes will include frequency of sunburns, use of sunless tanning products, and sun protection behavior.

## Methods

### Study design

This study is a cluster randomized trial design where data collection will occur simultaneously in two public beach locations located in eastern Massachusetts. The Departments of Public Works in the cities of Revere and Hull, Massachusetts have granted permission for study activities to be conducted at these beach sites. All study procedures and materials were approved by the University of Massachusetts Medical School's Institutional Review Board (IRB).

### Eligibility criteria

In order to capture the most natural, representative sample, few exclusion criteria will be imposed. Participants must be female and ages 18–75, English speaking, able to read at the 6^th ^grade level, and willing to participate. The proposed study will exclude individuals below the age of 18 because childhood sun protection and exposure behaviors are associated with different etiological influences than adult behavior, namely parental influences. Even though adolescents under 18 represent a high-risk group and may have some autonomy from parents regarding their sun protection behavior, the degree to which sunless tanning products appropriately address the variables contributing to their intentional sun exposure has not been addressed in the literature. Non-English speaking individuals will be excluded because the measures we propose to use have not been validated for use in other languages. Participants also have to be willing and able to provide at least two of the following: home phone, work phone, mailing address, home email, or work email, so they could be contacted for the follow-up assessments.

### Randomization

Beach locations (Revere and Nantasket Beaches in Massachusetts, US) will be randomly assigned to either intervention or control condition on each day of data collection during the month of July. Randomizing by beach location prevents contamination of conditions while holding weather conditions and day constant across groups. Weekend and weekdays will be balanced across locations and conditions, given that weekend beach visitors may have different characteristics than weekday beach visitors.

### Recruitment, screening process and informed consent

At both intervention and control beaches an unmarked tent will be set up in a central location during peak UV hours (11 a.m. to 4 p.m.) [34], on week and weekend days in which inclement weather was not forecasted. Research assistants will approach female sunbathers and ask them if they would like to participate in a study on sunbathing. If the sunbather is interested, eligibility will be assessed during this initial contact.

Eligible and interested individuals will then go to the study tent where participants will receive a verbal description of the study and be asked to read and sign an informed consent form. Upon providing informed consent, all participants, regardless of condition, will complete questionnaires. Participants, depending on the beach randomization, will then complete one of the two conditions.

### Outcomes and study measures

The primary outcome is sunbathing. Participants will be asked how much time they spent in the sun with the intention of getting a tan in the past month using a 9-point scale where 0 = never, 1 = once, 2 = twice, 3 = once a month, 4 = twice a month, 5 = once a week, 6 = twice a week, 7 = almost every day and 8 = everyday. The wording of this item is based on recommendations made by Glanz and colleagues 2008 [35]. However, the response options will be tailored to one month's time. This measure will be implemented at baseline, which will reflect sunbathing in the month previous to our contact with them at the beach, at 1-month follow-up to reflect sunbathing in the month following our contact with them at the beach, and at 12-months to reflect their sunbathing during one month of the following summer.

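### The primary outcome is defined and powered in hours of sunbathing per week, but is measured with a frequency item whose categories overlap

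*Protocol article*

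**What the plan says.** The abstract (Methods and Design) states: "The primary outcome is average sunbathing time per week". The Sample size section repeats this as "the primary outcome: average time spent sunbathing per week", and Table 1 is titled "Sample size for three test scenarios for primary outcome: hours spent sunbathing per week". The planning difference "is assumed to be 0.75 and 0.70 hours sunbathing per week at 1 and 12 months", set against a control mean of 2.10 with SD 2.0.

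Outcomes and study measures describes one item for the primary outcome. Participants are asked "how much time they spent in the sun with the intention of getting a tan in the past month using a 9-point scale". The options start at 0 (never), 1 (once) and 2 (twice) and continue "3 = once a month, 4 = twice a month, 5 = once a week, 6 = twice a week, 7 = almost every day and 8 = everyday". "This measure will be implemented at baseline", and again at 1 and 12 months. The section gives no question on session length and no rule for turning codes into hours.

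The text on the primary hypothesis, at the end of Longitudinal analyses, enters sunbathing directly as the outcome of a linear mixed model.

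The wording is not uniform. The abstract also gives the aim as a reduction in how often participants sunbathe. Research goals and the outcomes section call the primary outcome simply sunbathing.

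**The concern.** The stem asks for an amount of time, but the answers count occasions. Hours per week is occasions multiplied by duration, and only the first factor is collected. If hours are the target, the item does not deliver them. If frequency is the target, the definition in the abstract and every planning figure in Table 1 are in the wrong unit.

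The response scale has a second defect. The options were adapted to a one-month recall, and over one month some of them coincide. The linear model treats the codes as evenly spaced and increasing, and they are neither.

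At stake are the meaning of the primary result and the relevance of the sample size.

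**Working it through.** **1. Which unit does the sample size use?** Inputs from the Sample size section and Table 1: SD 2.0 hours, differences 0.75, 0.70 and 0.72 hours, ICC 0.01, cluster sizes 12, 14 and 9, dropout 15%, 25% and 25%, 5% significance and 80% power. I take the test as two-sided, which the article does not state.

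Formula (baseline-adjusted comparison with r follow-up measures):

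n per arm = 2 × [SD × (1.96 + 0.8416) / difference]² × {[1 + (r − 1)ρ]/r − ρ²}

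This is multiplied by 1 + (m − 1) × 0.01 for clustering. The total is 2n / (1 − dropout).

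- Row A (r = 1, ρ = 0.50): 111.63 × 0.75 = 83.7, so 84. Then 84 × 1.11 = 93.2, so 94. 188 / 0.85 = 221.2, so **222**, as printed.
- Row B (r = 1, ρ = 0.45 from the text): 128.14 × 0.7975 = 102.2, so 103. With m = 14, 103 × 1.13 = 116.4, so 117 and a total of 312. With m = 118/8 = 14.75, 103 × 1.1375 = 117.2, so 118 and a total of 314.7. The table prints 118 and **314**. With ρ = 0.50, as printed in the table, the row does not reproduce (110 to 111 per arm, total 293 to 296).
- Row C (r = 2, ρ = 0.50): 121.12 × 0.50 = 60.6, so 61. Then 61 × 1.08 = 65.9, so 66. 132 / 0.75 = **176**, as printed.

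The arithmetic is sound, and it rests on hours per week with an SD of 2.0 hours.

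**2. What do the codes measure?** Take a month as 30.4 days and read almost every day as 25 days (my assumption). The documents give no session length, so I show a range of 0.5 to 4 hours.

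| Code | Option | Occasions per month | Per week | Hours/week at 0.5 h | at 1 h | at 4 h |
|---|---|---|---|---|---|---|
| 1 | once | 1 | 0.23 | 0.12 | 0.23 | 0.92 |
| 2 | twice | 2 | 0.46 | 0.23 | 0.46 | 1.84 |
| 3 | once a month | 1 | 0.23 | 0.12 | 0.23 | 0.92 |
| 4 | twice a month | 2 | 0.46 | 0.23 | 0.46 | 1.84 |
| 5 | once a week | 4.3 | 1 | 0.5 | 1 | 4 |
| 6 | twice a week | 8.7 | 2 | 1 | 2 | 8 |
| 7 | almost every day | 25 | 5.76 | 2.88 | 5.76 | 23.0 |
| 8 | every day | 30.4 | 7 | 3.5 | 7 | 28 |

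For any code above 0, the hours vary eightfold with the assumed session length. At code 5 the spread is 3.5 hours per week, against a target difference of 0.70 hours.

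**3. What does a mean difference in codes stand for?** Suppose 70% of participants move up one step, a mean shift of 0.70 codes, at 1 hour per session:

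- codes 1 to 2: 0.70 × (0.46 − 0.23) = +0.16 h/week
- codes 2 to 3: 0.70 × (0.23 − 0.46) = −0.16 h/week
- codes 5 to 6: 0.70 × (2 − 1) = +0.70 h/week
- codes 6 to 7: 0.70 × (5.76 − 2) = +2.6 h/week

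The same coded difference can be a small increase, a small decrease or a large increase. Counting occasions instead of hours changes the units but not the pattern.

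**4. Power on the measured scale.** The documents give no mean, SD or target difference in scale points, so no corrected sample size can be computed. To show the dependence only, take N = 250, 25% loss (93.75 per arm), ρ = 0.45, a design effect of 1 + (93.75/8 − 1) × 0.01 = 1.107, the baseline to 12-month comparison, and a difference of 0.70 points:

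| Assumed SD (points) | Power |
|---|---|
| 1.5 | 0.93 |
| 2.0 | 0.72 |
| 2.5 | 0.53 |
| 3.0 | 0.40 |

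Both the SDs and the 0.70-point difference are assumptions.

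**The case against.** The best defence is that frequency is the intended outcome. The abstract states the aim as reducing how often people sunbathe, two sections say only sunbathing, and the outcomes section operationalises it as frequency. The intervention offers a substitute for sunbathing, so the number of occasions is a natural target. On that reading the trial measures what it wants, and the error lies in the units of the abstract's outcome statement and of Table 1. This stands: frequency is a legitimate endpoint. It does not remove the conflict, because the abstract and the Sample size section still name hours per week as the primary outcome.

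A reader might infer that the trial cannot estimate its primary outcome at all, or that missing an effect on session length is a flaw in itself. Both hold only if hours are the intended target, and the article does not settle that.

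It can also be said that this is a condensed article and that a fuller document might contain a duration item. That is possible. But this section fixes the item, its coding, its recall period and all three time points, so the issue is two conflicting statements, not omitted detail. The article's general allowance for generalized mixed models with discrete outcomes does not help either: the primary hypothesis is assigned a linear model, and no choice of model makes overlapping options distinct.

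**Conclusion.** The point holds as an internal contradiction on the primary outcome. The planning figures are correct on the hours scale, but the item described does not yield hours. The stated power therefore does not carry over to the measured variable, where it is unknown and could be higher or lower than planned. A reader might infer from the illustration above that the trial is underpowered because of this mismatch; the documents do not support that, since they give no SD or target difference in scale points.

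Separately, the nine codes are not monotone over a one-month recall and are unequally spaced, so a linear mixed model on raw codes gives a difference without a stable meaning. This follows from the option labels and needs no assumption about session length.

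The mismatch does not by itself bias the comparison between arms. It damages the interpretation of the primary result and the relevance of the sample size, and it should be resolved before the outcome is used. The conclusion assumes that no duration item exists outside this article.

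**What to change.** Choose one of two routes and make the abstract, Outcomes and study measures, Sample size and Table 1 agree.

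(a) **Keep hours per week.** At baseline, 1 month and 12 months, ask for the number of days in the past month spent in the sun to get a tan, and the usual hours on such a day. Derive hours per week = days × hours / (days in the month / 7) and name this the primary outcome. Table 1 then stays in the right unit. Cost: one item becomes two at each time point, the wording departs from the published recommendation on which the current item is based, recall burden rises somewhat, and the variable will be skewed.

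(b) **Declare frequency the primary outcome throughout.** Merge or replace the overlapping options, or ask the number of days directly. Analyse occasions per month, not raw codes. Restate the Table 1 mean, SD and difference, and the power, in that unit. Cost: new planning values are needed, the sample size may change, and effects on session length fall outside the primary outcome.

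Relabelling the present 9-point code as a frequency score is not enough, because the duplicated categories would remain in the primary endpoint.

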More specifically, the primary hypothesis will be tested using a linear mixed model with group (intervention, control) as a between subjects factor (fixed effect) and time (baseline, 1 month, and 1 year follow-up) as a within subjects factor. Sunbathing is the primary outcome variable. Secondary outcome variables including sun protection behavior, sunburns, and use of sunless tanning products will be examined in the same way. Because these dependent variables appear to be associated with different motivating variables, they are likely to be conceptually distinct and will be analyzed in separate models. Age will be entered as a covariate in both models because these factors are typically associated with the outcome variables [42]. Significant group by time interactions would be consistent with the primary hypothesis, such that the intervention group would engage in higher rates of sun protection and lower rates of sun exposure than the control group at 1- and 1-year follow-up, but not baseline. In exploratory analyses, ethnicity (White, nonwhite), and age will be entered as factors in the original model to determine differential response by these factors.

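### Two pairs of response options on the past-month sunbathing item mean the same thing but are scored two points apart, so the low end of the primary score is out of order

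*Protocol article*

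**What the plan says.** Outcomes and study measures in the protocol article defines the primary outcome by a single item. Participants report "how much time they spent in the sun with the intention of getting a tan in the past month using a 9-point scale". After 0 for never, the low codes are "1 = once, 2 = twice, 3 = once a month, 4 = twice a month" and the high codes are "5 = once a week, 6 = twice a week, 7 = almost every day and 8 = everyday".

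The article says that the wording follows a published recommendation and adds: "However, the response options will be tailored to one month's time". The one-month window applies at all three assessments: the month before the beach contact, the month after it, and "at 12-months to reflect their sunbathing during one month of the following summer".

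Under Longitudinal analyses, "the primary hypothesis will be tested using a linear mixed model with group (intervention, control) as a between subjects factor", and sunbathing is named as the outcome of that model. The same section assigns linear mixed models to continuous outcomes and generalised linear mixed models to discrete ones. No rule for merging or recoding response options is given.

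**The concern.** Labels such as *once* and *once a month* can be told apart when the recall period is a season or a year. When the recall period is one month they cannot, and the same goes for *twice* and *twice a month*. A respondent with one or two occasions has two correct answers to choose from, scored two points apart.

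This matters because a linear mixed model uses the numeric codes as they stand. The choice between equivalent labels enters the primary outcome as error. Some true reductions in sunbathing would be recorded as no change or as an increase. The fault also lies where an effective intervention would move some women, from weekly sunbathing down to one or two occasions in the month.

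**Working it through.** The plan states no figure on this point that could be reproduced. The check is whether the codes rise with the behaviour they describe.

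**Inputs.** The recall window and the nine labels come from Outcomes and study measures. Two assumptions are added: the month has 28, 30 or 31 days, and *almost every day*, which the article does not quantify, means 60% or 90% of days.

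**Conversion.** Weekly labels are multiplied by (days in month)/7. For 30 days, 30/7 = 4.29 and 2 × 30/7 = 8.57.

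| Code | Label | Occasions in a 30-day month |
|---|---|---|
| 0 | never | 0 |
| 1 | once | 1 |
| 2 | twice | 2 |
| 3 | once a month | 1 |
| 4 | twice a month | 2 |
| 5 | once a week | 4.29 |
| 6 | twice a week | 8.57 |
| 7 | almost every day | 18 to 27 (assumed) |
| 8 | everyday | 30 |

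**Pairwise check.** Nine codes give 9 × 8/2 = 36 pairs.

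- Ties: codes 1 and 3 (one occasion each) and codes 2 and 4 (two occasions each).
- Inversions: one. Code 2 means two occasions and code 3 means one.
- The other 33 pairs are correctly ordered.

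The result is the same for all three month lengths and for both assumptions about *almost every day*.

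**Consequences for the score.**

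- Same behaviour, different label: 3 − 1 = 2 points, or 4 − 2 = 2 points. As a share of the range, 2/8 = 25%.
- A fall from two occasions to one: from code 2 to code 3 the score rises by 1; from 2 to 1 or from 4 to 3 it falls by 1; from 4 to 1 it falls by 3.
- A fall from once a week to two occasions: 5 − 4 = 1 point or 5 − 2 = 3 points, depending only on the label ticked.

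**Can this be turned into a loss of power?** Suppose a fraction q of women with a given low frequency tick the higher of the two equivalent codes. Label choice then adds a variance of 2² × q(1 − q) = 4q(1 − q) among those women. At q = 0.5 this is 1, its maximum; at q = 0.2 it is 0.64. Both are in squared scale points. Going further needs the share of women with one or two occasions, the value of q, the consistency of a woman's choice from visit to visit, and the SD of the 0–8 score. The article gives none of these. The SD of 2.0 and the difference of 0.70 in Sample size and its Table 1 are in hours per week and cannot be combined with scale points.

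**The case against.** **The list may be the untailored source scale.** The tailoring sentence follows the list and is in the future tense, so the options actually used might differ. This leaves some doubt about the final form. But the sentence holding the list ties it to the past month, and the article gives no other list. The Sunburns item uses the same one-month window and runs in strict order from not at all to five times or more, so an orderly one-month scale was within reach.

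**Respondents may read the later labels as a habitual rate.** Some may. The question asks about the past month, though, and if some women answer with a count and others with a habit, the item is still ambiguous.

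**A recoding rule belongs in the full protocol or analysis plan.** That is fair, and its absence from an article is not the point. The point is that the scale, as stated, is wrong. The staff review of questionnaires described under Study operations would not catch it, because either label is a valid answer.

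**The fault is narrow.** This stands. A reader might infer that the primary score as a whole is unordered, but the disorder is confined to codes 1 to 4. Participants are sunbathers approached on the beach in July, and many may fall in codes 5 to 8.

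**A false treatment effect is not shown.** This also stands. A reader might infer that the labels could create a spurious benefit. Both arms answer the same item, and nothing in the article suggests that the intervention would alter the choice between *once* and *once a month* when behaviour is unchanged.

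**Conclusion.** The point holds for the scale as printed. In a one-month window the primary item has two tied pairs of codes and one inversion, all within codes 1 to 4. The same behaviour can differ by 2 points (25% of the range), and one path from two occasions to one raises the score. These facts rest only on the printed labels and the stated window.

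The likely consequence is mainly non-differential measurement error and reduced sensitivity to real change. Baseline is completed at the beach and follow-up by email, mail or phone (Recruitment, screening process and informed consent; Retention), so a woman's choice of label may vary between visits, although the article does not show that it would.

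It is tempting to compare the 2-point artefact with the 0.70 difference, or to add its variance to the SD of 2.0 and quote a loss of power. The documents do not support either step: the units differ, and no response distribution is given. The size of the effect on the treatment comparison is unknown.

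**What to change.** Remove options 3 and 4, leaving seven strictly ordered levels: never, once, twice, once a week, twice a week, almost every day, everyday.

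If forms are already in use, specify before analysis that code 1 is pooled with 3 and code 2 with 4, and rescore the seven resulting levels 0 to 6 in order, in the same way at baseline, 1 month and 12 months. Because the pooled codes describe the same behaviour, no information on frequency is lost. If the options actually used differ from the printed list, state them.

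The cost is a change to the questionnaire or a short recoding rule. Some comparability with the source scale is lost, but its options are already being altered. The change restores order only; it does not make the steps between levels equal.
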